### Current study

In sum, the current protocol describes a study that will be conducted to examine the effectiveness of a classroom-based program promoting a prosocial classroom climate (i.e., Meaningful Roles). Figure 1 presents the conceptual model of the research design. A cluster RCT will be performed to investigate if the program results in more prosocial classrooms (e.g., more prosocial behavior, more cooperation, less conflict). The program will be compared to a control condition. We will use a multi-informant (children, teachers, and school leaders) and multi-method (questionnaires and focus groups) design. As illustrated in Fig. 1, it is expected that Meaningful Roles will increase children’s social autonomy, social competence, and social relatedness, resulting in an increase in intrinsic (prosocial) motivation and a prosocial classroom climate (i.e., increased prosocial behavior, positive teacher attitudes, civic skills, and school wellbeing, and reduced bullying and bullying victimization). In addition, the second aim is to examine moderators of effectiveness. This is important because it is likely that Meaningful Roles is not equally effective across child, teacher, school, and program characteristics (i.e., program integrity). The final aims of this study are to evaluate the working elements of Meaningful Roles (i.e., meaningful roles, classroom meetings, and compliments) and to evaluate how the program is experienced by teachers and school leaders.

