### Data collection

Online questionnaires assessing demographics (e.g., age, gender), primary outcomes (i.e., prosocial behavior, intrinsic prosocial motivation, social competence, social autonomy, and social relatedness) and secondary outcomes (i.e., school wellbeing, social position, and antisocial behavior) will be completed by children prior to the start (T1) of the program. Halfway through the program (T2) and after completion of the program in the intervention condition (T3), children complete questionnaires about program content (i.e., working elements) in addition to questionnaires assessing primary and secondary outcomes. Teachers complete questionnaires about demographics (e.g., age, years of experience), attitudes, and civic skills at T1 and questionnaires about attitudes, civic skills, program content (to assess program integrity), and program evaluation at T2 and T3. Additionally, one teacher from each school will participate in the focus groups (at T1, T2, and T3), to evaluate the implementation of the program (i.e., qualitative information). Table 1 presents an overview of the instruments at each assessment point.

**Table 1 Tab1:** Overview of the variables’ instruments and sources

Outcome	Variable name	Instrument	Time of measurement	Variable type	Source
Primary outcomes					
Prosocial behavior	Injunctive norm	Developed for this study	T1, T2, T3	Outcome	Child
	Prosocial behavior (individual)	Based on the Strengths and Difficulties questionnaire (SDQ), subscale prosocial behavior	T1, T2, T3	Outcome	Child
	Prosocial behavior (according to classmates)	Sociometric nominations	T1, T2, T3	Outcome	Child
	Cooperation in the classroom	Classroom Peer Context Questionnaire (CPCQ), subscale cooperation	T1, T2, T3	Outcome	Child
	Conflict in the classroom	Classroom Peer Context Questionnaire (CPCQ), subscale conflict	T1, T2, T3	Outcome	Child
Intrinsic (prosocial) motivation	Social goals	Developed for this study	T1, T2, T3	Outcome	Child
Social competence	Self-esteem	Developed for this study, based on de Rosenberg Self-Esteem Scale	T1, T2, T3	Outcome	Child
Social autonomy	Social autonomy and responsibility	Developed for this study, based on the School as a Caring Community Profile – II and Child Development Project [34]	T1, T2, T3	Outcome	Child
Social relatedness	Comfort and cohesion	Classroom Peer Context Questionnaire (CPCQ), subscale comfort and cohesion	T1, T2, T3	Outcome	Child
Secondary outcomes					

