### Statistical analyses

Before the analyses, possible baseline (T1) differences in demographics and outcome variables (baseline assessment) between children in the intervention program and the control condition will be checked with ANOVA (continuous variables) and chi-square analyses (categorical variables). To investigate the effectiveness of the intervention program, regression analyses will be performed. The dependent variables are the outcome measures at intermediate (T2) or posttest (T3), condition is the predictor variable (1 = intervention, 0 = control), and baseline (T1), potential differences between the experimental and control group at T1, or intermediate measures (when dependent variables are the outcome measures at T2) are the covariates. The effect of potential moderators (categorial or continuous) on the outcomes will be examined by adding interaction effects to the models.

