## Discussion

This study protocol presents the design of a cluster RCT to investigate the effectiveness of a classroom-based program, Meaningful Roles, to promote a more prosocial classroom climate in primary schools, through improving intrinsic motivation to behave prosocial, by enhancing SDT components (i.e., social autonomy, social competence, and social relatedness). This is important, because a positive, prosocial classroom climate is associated with an optimal learning environment, as well as positive school quality and wellbeing in children [1, 2]. Previous research showed improved prosocial classroom climate (e.g., increased prosocial behavior) in youth after receiving school- or classroom-based social-emotional focused programs (e.g., [11, 15]), as well as improved psychological health after receiving programs focused on STD components [22]. To overcome limitations of previous research, including suboptimal study design (e.g., non-randomization) and target group (e.g., US samples), we will examine a classroom-based approach for upper primary school students and use a cluster RCT to exclude confounding (e.g., allocation and selection bias) as much as possible. We will use a multi-informant (i.e., child, teacher, school leader) and multi-method (i.e., questionnaires and focus groups) approach. Moreover, we strive to use a large, diverse sample, that could allow us to examine potential moderators of program effectiveness (i.e., child, teacher, school, and program characteristics, i.e., working elements and program integrity).

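### The protocol hypothesises that climate improves through the three needs and motivation, but the described regressions estimate only condition effects, and the rule for T2 covariates could strip out part of the program effect

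*Protocol article*

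**What the plan says.** **The hypothesis.** In the protocol article, Background, Current study, the program is expected to raise the three needs, "resulting in an increase in intrinsic (prosocial) motivation and a prosocial classroom climate". The Discussion repeats the mechanism: climate is to improve "through improving intrinsic motivation to behave prosocial, by enhancing SDT components". The Methods paragraph of the abstract describes the same chain.

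**The aims.** Current study lists effectiveness ("A cluster RCT will be performed to investigate if the program results in more prosocial classrooms"), then moderators ("In addition, the second aim is to examine moderators of effectiveness"), then the components and the users' experience ("The final aims of this study are to evaluate the working elements of Meaningful Roles" and so on).

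**The data.** Children complete questionnaires at T1 and again "Halfway through the program (T2) and after completion of the program in the intervention condition (T3"). Table 1 lists all three needs, motivation and the child-reported behavior and climate measures at T1, T2 and T3. It types the needs and motivation only as outcomes.

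**The analysis.** "To investigate the effectiveness of the intervention program, regression analyses will be performed". The dependent variable is the outcome at T2 or T3, and "condition is the predictor variable (1 = intervention, 0 = control"). The covariates are the baseline measure, variables that differ between arms at T1, and, for dependent variables measured at T2, intermediate measures. Moderators enter as interactions. No model relates a need to motivation, or either of them to behavior or climate.

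**The concern.** There are two linked problems in the Statistical analyses section.

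1. **The models do not bear on the word *through*.** Suppose every planned regression came out in favour of the program. That would fit a program that works by meeting the three needs. It would fit equally well a program that moves needs and climate by unrelated routes, for example by general attention to the class. A conclusion that climate improved through the needs and motivation would not be supported by the described models.

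2. **The covariate rule for T2 is garbled, and its likely meaning is harmful.** T2 is measured after randomisation and halfway through the program. If T3 outcomes are adjusted for T2 measures, the condition coefficient is no longer the effect of the program. It omits what had already been achieved by T2 and carried forward, which is the pathway the hypothesis relies on.

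**Working it through.** **Step 1. Can condition-only regressions separate the two explanations?** Let condition raise a need by *a*, and let a unit of need raise the outcome by *b*. Take *a* = 0.21 (the effect size in Study sample) and *b* = 0.5 (an assumption).

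- Through the need: effect on the need 0.21, effect on the outcome 0.21 × 0.5 = 0.105.
- Unrelated routes: effect on the need 0.21, need-to-outcome slope 0, direct effect on the outcome 0.105.

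Regressing each variable on condition returns 0.21 and 0.105 in both cases. The regressions do test a necessary link: if the needs do not move, the mechanism is undermined. They do not test whether the need carries the effect.

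**Step 2. What does T2 adjustment do to a T3 effect?** Read literally, the rule puts T2 measures on both sides of a T2 model, so it cannot be what is meant. If T3 is meant, let δ2 and δ3 be the condition effects at T2 and T3 given the same T1 covariates, and let β be the slope of T3 on T2 in the model with condition and T1. For least squares in the same children,

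adjusted coefficient = δ3 − β × δ2.

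The article gives neither β nor the wave to which 0.21 applies. With δ2 = δ3 = 0.21 and an assumed range for β:

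| β | Adjusted coefficient | Share removed |
|---|---|---|
| 0.3 | 0.21 − 0.063 = 0.147 | 30% |
| 0.5 | 0.21 − 0.105 = 0.105 | 50% |
| 0.7 | 0.21 − 0.147 = 0.063 | 70% |

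If only half the effect is present at T2 (δ2 = 0.105) and β = 0.5, the coefficient is 0.21 − 0.0525 = 0.1575, so 25% is removed.

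**Step 3. How far would the data support a mediation analysis?** The chain has three stages after randomisation (needs, motivation, climate) but only two post-baseline waves. At least two stages must share a wave, so part of the order cannot be tested.

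**Step 4. Does the stated power carry over?** The plan's own figure is 42 schools for power 0.80, alpha 0.05 and effect size 0.21. Ignoring clustering, n per arm = 2 × (1.960 + 0.842)² / 0.21² = 356 (two-sided). With *m* pupils per school, 21 schools per arm give 80% power when 1 + (m − 1) × ICC = 21m / 356. That is an ICC of about 0.010 at m = 20 and about 0.050 at m = 100. The article gives neither m nor ICC, so 42 can be neither confirmed nor refuted.

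That figure concerns the condition contrast. An indirect effect also needs the need-to-outcome path. Condition varies only between 42 schools, so the relevant slope may be the between-school one. By Fisher z, the expected statistic is atanh(r) × √(42 − 3):

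- r = 0.08: 0.0802 × 6.245 = 0.50, power about 0.08.
- r = 0.30: 0.3095 × 6.245 = 1.93, power about 0.49.
- Power 0.80 needs atanh(r) = 2.80 / 6.245 = 0.449, so r is about 0.42.

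These correlations are assumptions. If within-class and between-school slopes were equal, pupil-level data would add information and power would be higher. The article does not settle that.

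**The case against.** The strongest reply is that no stated objective is left without an analysis. The listed aims are effectiveness, moderators, working elements and experience. A program built on a theory, with a conceptual model, does not oblige a mediation test, and the article promises no mediated conclusion. It is also a condensed article: an exploratory mediation model could sit in a fuller protocol or analysis plan that is not shown.

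Most of this stands, and it limits the point. Four stronger readings are tempting and are not supported:

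- *A stated aim has no analysis.* Mediation is not among the aims.
- *The mechanism cannot be tested in this trial.* That is true of the described models, not of the data. The needs and motivation are measured at all three waves, and regressing them on condition already tests one necessary link.
- *T2 serves only as a second endpoint.* Intermediate measures are also named as covariates.
- *A mediation test would be well powered with the planned sample.* Pupils per school are not given, and only 42 schools carry the condition contrast.

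The reply does not remove two things. The article assigns the needs and motivation a role in Table 1, outcome only, that does not match its causal model. And the T2 covariate rule is a statement in the text that is wrong as written, not something left to another document.

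**Conclusion.** The point holds in limited form. The described models give condition effects on each measure, conditional on covariates, and tests of moderation. They do not support a conclusion that climate changed through the needs or motivation. This follows from the text and rests on no numerical assumption.

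The T2 covariate rule must be corrected whatever is decided about mediation. If it means T3 outcomes, the loss is β × δ2: between 30% and 70% of a 0.21 SD effect held from T2 to T3 for β of 0.3 to 0.7, and less if the effect builds up late. Those slopes are assumptions. That the coefficient shrinks requires only a positive effect at T2 and a positive slope.

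Neither problem changes the sample size or the randomised comparison itself, provided the total-effect models are adjusted only for variables measured before the program.

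**What to change.** 1. **Correct the covariate sentence.** State that the total-effect models for both T2 and T3 outcomes adjust for T1 measures and for no T2 measure.
2. **Prespecify one secondary, exploratory mediation analysis.** Condition → T2 autonomy, competence, relatedness and motivation → T3 prosocial behavior, cooperation and conflict. Adjust for T1 mediator and T1 outcome, model clustering by school and class, separate within-school from between-school paths, and report an interval for the indirect effect. State that needs and motivation share a wave, so their order is not tested.
3. **Tie the wording to the result.** Without a supported indirect effect, limit conclusions to total effects on each measure.

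The cost is a wording change and modest analyst time, with no new data collection. The downside is that the mediator-to-outcome link is not randomised, so the mediation result stays exploratory. Its power is uncertain with 42 schools, so an inconclusive interval should not be read as evidence against the mechanism. Specifying the model in advance matters because several needs and outcomes would otherwise allow many post-hoc choices.

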## Methods

### Design

A cluster RCT will be conducted. Schools will be randomized (stratified for number of participating classrooms) into the intervention condition in which the program starts immediately or into a control condition that receives the program one school year later (see Fig. 2), using an online randomization tool [33] in a 1:1 ratio. We will recruit a diverse sample of children from primary schools in the Netherlands.

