### Study sample

We aim to include *N* = 42 schools to ensure there is enough power for the analyses (*N* = 21 schools for both the intervention and waitlist control condition). This sample size is sufficient to examine the effectiveness of Meaningful Roles and potential moderators, with a power of 0.80, an alpha of 0.05 and a medium effect size of 0.21 [18].

Participants are children from the upper grades of primary school (grades 5–8) in the Netherlands, their teachers (who will implement the program) and school leaders. The children will mostly be between 8 and 12 years old.

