### Instruments

#### Primary outcomes

*Prosocial behavior* will be measured by several instruments measuring different domains (i.e., injunctive norm, individual prosocial behavior, sociometric nominations, cooperation in the classroom and conflict in the classroom).

Prosocial behavior as an injunctive norm (i.e., children’s attitudes towards prosocial behavior that are on average held in the classroom; [35]) will be assessed with three items specifically developed for this study (i.e., What can make you popular in your class?: “Helping each other”, “Being nice to each other” or “Working together”), rated on a 3-point scale from 1 (*not true*) to 3 (*definitely true*). Higher scores reflect a higher injunctive norm of the group towards prosocial behavior.

Individual prosocial behavior will be measured with the subscale prosocial behavior of the Strengths and Difficulties Questionnaire (SDQ), Dutch version [36], adapted for the current study. Four items are used (e.g., “I try to be nice to my classmates”), rated on a 4-point scale from 1 (*never*) to 4 (*always*). The SDQ-Dutch has sufficient psychometric properties in a children sample, with a Cronbach’s alpha of 0.78 for the total scale and 0.62 for the prosocial subscales [37]. Higher scores reflect more prosocial behavior.

Prosocial behavior according to children’s classmates will be measured with sociometric nominations. For each question, children see a list with the names of all classmates and select the classmates that fit the question best according to them [38]. Two items are used (i.e., “Which classmates help you with assignments (for example with math or language)?” or “Which classmates help you with problems (for example, when you are sad)?”). For each child, the number of received nominations was divided by the number of possible nominations (i.e., number of classmates), resulting in a proportion score for prosocial relations [39].

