Cooperation and conflict in the classroom will be measured with the Classroom Peer Context Questionnaire (CPCQ), subscales cooperation and conflict, respectively [38, 40], rated on a 4-point scale ranging from 1 (*not true*) to 4 (*completely true*). The cooperation subscale consists of four items assessing the extent to which children experience positive behavior (e.g., “In this classroom, children help each other”). The conflict subscale consists of four items assessing the extent to which children experience negative behavior. For the current study, two items are used (i.e., “In this classroom, children are unkind to each other” and “In this classroom, children bully each other”). The CPCQ has adequate psychometric properties in a children sample, with a Cronbach’s alpha of 0.79 and 0.83 for the cooperation and conflict subscale, respectively [38]. Higher scores on the cooperation subscale reflects more positive behavior, while for the conflict subscale it reflects more negative behavior.

*Intrinsic (prosocial) motivation* will be measured with four items specifically developed for this study (e.g., “I think it is important to help someone” or “I want to know how to be a good friend”), rated on a 3-point scale ranging from 1 (*not true*) to 3 (*definitely true*). Higher scores reflect more intrinsic (prosocial) motivation.

*Social competence* will be measured with items based on the Rosenberg Self-Esteem Scale (RSES), Dutch version [41, 42]. Five items are used (e.g., I think positively about myself), rated on a 3-point scale ranging from 1 (*not true*) to 3 (*definitely true*). The Dutch RSES showed high internal consistency in adults [41] and sufficient psychometric properties in adolescent samples [43, 44]. Higher scores reflect more perceived social competence.

*Social autonomy* will be measured with items based on the School as a Caring Community Profile-II (SCCP-II; (Lickona and Davidson. School as a caring community Profile II, unpublished)) and the Child Development Project [34, 45]. Five items are used (e.g., “In this classroom, children help with making group appointments” or “In this classroom, you can choose how you want to do something”), rated on a 4-point scale ranging from 1 (*never*) to 4 (*always*). Higher scores reflect more social autonomy.

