*ocial relatedness* will be measured with items of the Classroom Peer Context Questionnaire (CPCQ), subscales comfort and cohesion [38, 40], rated on a 4-point scale ranging from 1 (*not true*) to 4 (*completely true*). The comfort subscale consists of four items assessing the extent to which children feel at ease in the classroom (e.g., “In this classroom, I can be myself”). The cohesion subscale consists of four items assessing the extent to which the children in the classroom spend time together. For the current study, two items are used (i.e., “In this classroom, everyone likes each other” and “In this classroom, everyone belongs to the group”). The CPCQ has adequate psychometric properties in a children sample, with a Cronbach’s alpha of 0.83 and 0.68 for the comfort and cohesion subscale, respectively [38]. Higher scores on both subscales reflect more positive behavior.

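### Baseline (T1) enters as a single covariate, most naturally the child's own score. Where school or class T1 slopes are steeper, adding the T1 class or school mean would recover precision at little cost

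*Protocol article*

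**What the plan says.** Design: "Schools will be randomized (stratified for number of participating classrooms"), 1:1, to immediate or delayed start. Study sample: the target is "42 schools to ensure there is enough power for the analyses", 21 per arm, "with a power of 0.80, an alpha of 0.05 and a medium effect size of 0.21". No ICC, cluster size or T1-to-follow-up correlation is given.

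Statistical analyses: "To investigate the effectiveness of the intervention program, regression analyses will be performed". The outcome at T2 or T3 is the dependent variable and condition is the predictor. The covariates are listed as "and baseline (T1), potential differences between the experimental and control group at T1", followed by intermediate measures. The section does not say whether T1 is the child's score, a class mean or a school mean, and it names no school or class term.

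Primary outcomes: Table 1 lists nine primary measures, all reported by children. Several ask the child to describe the class:
- the injunctive norm asks "What can make you popular in your class" and is defined as an average attitude in the class
- cooperation has items such as "In this classroom, children help each other"
- conflict and social autonomy are worded in the same way
- cohesion has "In this classroom, everyone belongs to the group"

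Cohesion is paired with comfort, which concerns the child's own ease in the class.

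**The concern.** Condition varies only between schools, so the precision of its effect depends on how much variation between schools the model removes. For a classroom-rated measure, one child's T1 score mixes class climate with that child's rating style. The slope on that score is largely a within-class slope. If it is flatter than the slope linking school or class T1 means to follow-up means, part of the baseline climate difference between schools stays in the residual. A chance T1 imbalance between the two sets of 21 schools is then only partly removed.

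A random-intercept or similar model does not cure this. Its single T1 slope lies close to the within-cluster slope, whereas ordinary regression gives the steeper pooled slope. The T1 means that would close the gap can be computed from data the trial already collects.

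**Working it through.** **The plan's own figure.** Without clustering, n per arm = 2 × (1.960 + 0.842)² / 0.21² = 356 (two-sided alpha assumed), or about 17 children per school (356/21). That does not lead to 42 schools. With clustering, 42 schools give power of about 0.80 only for particular unstated pairs, such as 40 children per school with ICC 0.032, or 60 with ICC 0.040. The figure can be neither reproduced nor refuted, and it supplies no inputs for what follows.

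**Method.** Let V be the variance of a school mean (the same at T1 and follow-up) and C the covariance of the T1 and follow-up school means. After adjustment with slope b, the school-level variance is V(1 + b²) − 2bC. The variance of the condition effect is 2/21 times that. It is smallest at b = C/V, the school-mean slope.

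**Worked scenario (all inputs assumed).** 4 classes of 18 children per school; variance 0.05 between schools, 0.15 between classes, 0.80 within class; T1-to-follow-up correlation 0.8 between schools and between classes, 0.4 within class.
- V = 0.05 + 0.15/4 + 0.80/72 = 0.0986
- C = 0.05 × 0.8 + 0.15 × 0.8/4 + 0.80 × 0.4/72 = 0.0744
- School-mean slope = 0.0744/0.0986 = 0.755
- Pooled child-level slope = 0.20 × 0.8 + 0.80 × 0.4 = 0.48

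| T1 adjustment | Slope | Adjusted variance | SE of effect | Power at 0.21 |
|---|---|---|---|---|
| Within-class slope | 0.40 | 0.0548 | 0.072 | 0.81 |
| Pooled slope | 0.48 | 0.0499 | 0.069 | 0.84 |
| School mean | 0.755 | 0.0424 | 0.064 | 0.90 |

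Power is from the noncentral t with 40 degrees of freedom, or 39 with the mean. It ignores the small cost of estimating the school-level slope, so 0.90 is slightly generous. Adding the mean cuts the variance by 1 − 0.0424/0.0548 = 23% against the within-class slope and 1 − 0.0424/0.0499 = 15% against the pooled slope.

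**Chance imbalance.** The standard error of the T1 difference between arms is √(2/21 × 0.0986) = 0.097, so an imbalance of 0.10 SD is ordinary. The part left uncorrected is (0.755 − 0.40) × 0.10 = 0.035 SD with the within-class slope, or (0.755 − 0.48) × 0.10 = 0.028 SD with the pooled slope. These are 17% and 13% of 0.21.

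**Range, two-level layout.** 60 children per school, ICC 0.05 to 0.20, all at school level, pooled slope as comparator:
- Between-school correlation 0.8, within-school 0.3 to 0.5: the variance without the mean is 1.10 to 1.33 times larger, a reduction of about 9% to 25% when the mean is added. At ICC 0.10 and within-school correlation 0.4, power goes from 0.76 to 0.84.
- Correlations 0.5 and 0.3: ratio about 1.03.
- Both correlations 0.5: ratio 1.00, no gain.
- With 20 children per school the ratio runs from 1.00 to 1.21.

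**Range, school-and-class layout.** Simulation with 4 classes of 18, between correlations 0.7 to 0.8, within-class 0.3 to 0.5, within-class slope as comparator: reductions of 1% to 29%. In the least favourable case power was 0.926 without the mean and 0.925 with it. One corner of the two-level grid goes further: ICC 0.20, correlations 0.8 and 0.3, within slope, 1 − 0.0873/0.1341 = 35%.

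**Bias.** In simulation (42 schools of 60, no true effect, 2000 trials), every estimator averaged close to zero. At ICC 0.10 with correlations 0.8 and 0.4, the SD of the estimate was 0.077 with the child's score alone and 0.070 with the school mean. With both correlations 0.5 the SDs were 0.092 and 0.093.

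**The case against.** The strongest reply is that the article fixes none of this. It calls T1 a covariate without giving its level, and splitting a baseline score into cluster mean and deviation is detail often left to an analysis plan. A reader might infer that the plan specifies a child-level model and rules out a cluster mean. The text does not go that far: its only explicit child-level wording concerns the preliminary baseline check. The child's own score is still the natural reading, because Table 1 gives the child as source of every primary measure and the moderator interactions include child age, gender, grade and ethnic identity. The covariate list is also stated, and no mean is in it.

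A reader might also infer that the effect estimate is biased. It is not. The 0.03 SD is a shift given one particular imbalance, and it averages out over randomisations.

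Nor is the precision loss an established fact. It needs a between-cluster slope steeper than the child-level one, and the document gives nothing to confirm that. Scenarios that set the between correlation well above the within correlation build the gain in, which is why the equal-slope case belongs in the range.

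Finally, five of nine classroom-rated measures is too generous a count, since comfort is largely self-report. Four and part of a fifth is fair.

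**Conclusion.** The point stands as a conditional efficiency gain. If T1 is entered only as the child's score, and if classroom climate is more stable between schools and classes than individual ratings are within them, the planned model uses its baseline data poorly for the outcomes closest to the trial's aim. Under the assumed inputs (ICC 0.05 to 0.20, between-cluster correlation 0.5 to 0.8, within-cluster 0.3 to 0.5) the variance reduction runs from nil to about 25% against a pooled slope. It reaches 29% against a within-class slope in the school-and-class layout. None of these inputs comes from the document. The calculations do not show that the trial is underpowered or that the planned adjustment is invalid.

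**What to change.** State the level at which T1 enters. In the T2 and T3 models that account for clustering, prespecify two T1 terms for child-reported outcomes, at least the classroom-rated ones: the class or school mean at T1, and the child's deviation from it. Choose class or school in advance; the figures above are for the school mean. Include both terms whatever the T1 difference tests show. Civic skills and teacher attitudes are reported by teachers and have no child deviation, so use the class-level T1 score there.

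The cost is one extra covariate from data already collected and about one of 40 school-level degrees of freedom. Where the slopes are alike there is little or no gain and almost nothing lost.

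### Some covariates are picked by child-level tests of T1 differences that ignore school clustering, and the randomisation stratifier is not in the covariate list

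*Protocol article*

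**What the plan says.** All references are to the protocol article.

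- **Design:** schools are the unit of allocation, 1:1, "stratified for number of participating classrooms".
- **Study sample:** 42 schools, that is "21 schools for both the intervention and waitlist control condition", "with a power of 0.80, an alpha of 0.05 and a medium effect size of 0.21".
- **Statistical analyses, first step:** the check covers "possible baseline (T1) differences in demographics and outcome variables (baseline assessment"), and differences "between children in the intervention program and the control condition will be checked with ANOVA (continuous variables) and chi-square analyses (categorical variables").
- **Statistical analyses, main model:** outcomes at T2 or T3 are regressed on condition. The listed covariates are the T1 measure, "potential differences between the experimental and control group at T1", and in some models an intermediate measure.

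The T1 measure is therefore fixed in advance, and only the second item depends on the T1 check. Number of participating classrooms is not listed. The nearest item is the number of participating grades, which the Moderators section gives as a school characteristic. It is a related quantity, but a different one.

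**The concern.** Three features of the stated rule are unsuitable for this design.

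1. **Wrong unit.** The check treats children as independent, although only 42 units were allocated. Chance differences between schools then look like differences between arms.
2. **Wrong criterion.** A covariate earns its place by predicting the outcome. A significant T1 difference measures imbalance and says nothing about prognosis. A strong predictor that happens to be balanced is left out, and an irrelevant variable that happens to differ is put in.
3. **Set fixed too late.** The final covariates are known only after T1 data have been seen, and they can differ between outcomes. With many outcomes at two follow-up times, the adjusted estimates may not share one model.

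The one design variable known before any data are seen, the stratification factor, is absent from a list that is otherwise explicit. If school size is related to the outcome, stratification has already balanced it across arms. A model without it leaves that variation in the error term, so standard errors are too large and precision is lost.

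**Working it through.** **Does the plan's own figure supply the missing inputs?** Inputs from Study sample: effect size 0.21, alpha 0.05 (two-sided assumed), power 0.80, 21 schools per arm.

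- Without clustering: n per arm = 2 × (1.960 + 0.842)² / 0.21² ≈ 356, and 356 / 21 ≈ 17 children per school.
- With m children per school, the design effect is DE = 1 + (m − 1) × ICC. Power of about 0.80 then needs 21m / DE ≈ 356. That holds for particular pairs only, such as m = 40 with ICC about 0.035, or m = 68 with ICC about 0.045.

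The 42 schools can therefore be neither confirmed nor refuted, and they fix neither m nor the ICC. Both must be assumed.

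**False-flag rate of the child-level check.** With no true difference, ignoring clustering understates the variance of the arm difference by the factor DE. Assuming a 5% threshold for the check:

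flag rate = 2 × [1 − Φ(1.96 / √DE)]

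Low end, m = 20 and ICC = 0.02: DE = 1 + 19 × 0.02 = 1.38; 1.96 / √1.38 = 1.67; rate 9.5%.

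High end, m = 100 and ICC = 0.10: DE = 1 + 99 × 0.10 = 10.9; 1.96 / √10.9 = 0.59; rate 55%.

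| Children per school | ICC 0.02 | ICC 0.05 | ICC 0.10 |
|---|---|---|---|
| 20 | 9.5% | 16% | 25% |
| 40 | 14% | 25% | 38% |
| 68 | 20% | 35% | 48% |
| 100 | 26% | 42% | 55% |

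Simulating 42 schools (20,000 runs) agrees: 19.8% at m = 68, ICC 0.02; 48.2% at m = 68, ICC 0.10; 16.1% at m = 20, ICC 0.05.

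**Adding classes within schools.** For classes of 20 and four classes per school, DE = 1 + 19 × (school ICC + class ICC) + 60 × school ICC. With one class per school the last term drops out.

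| School / class ICC | DE, four classes | Rate | DE, one class | Rate |
|---|---|---|---|---|
| 0.01 / 0.04 | 2.55 | 22% | 1.95 | 16% |
| 0.02 / 0.05 | 3.53 | 30% | 2.33 | 20% |
| 0.05 / 0.05 | 5.90 | 42% | 2.90 | 25% |
| 0.05 / 0.10 | 6.85 | 45% | 3.85 | 32% |

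These lie inside the two-level range. For any positive ICC with more than one child per school, DE exceeds 1 and the rate exceeds 5%.

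**Effect on the test of the intervention.** This is a separate quantity. One simulation assumed 42 schools, four classes of 20, 20 T1 variables of which six were prognostic, and no intervention effect. School means of covariate-adjusted residuals were compared by t-test, with 1,000 runs per setting.

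| School / class ICC | T1 outcome only | Flagged covariates added |
|---|---|---|
| 0.01 / 0.04 | 5.9% | 4.5% |
| 0.05 / 0.05 | 4.8% | 3.7% |
| 0.05 / 0.10 | 4.8% | 3.5% |

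The Monte Carlo standard error near 5% is √(0.05 × 0.95 / 1,000) ≈ 0.7 percentage points. Adjusting before comparing arms can itself be conservative. I read this as no sign of inflation, not as proof that the rule is conservative.

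**The case against.** **The size rests on assumptions.** This stands. No ICC or school size is given, so no single rate can be stated as fact. Nor should one rate be multiplied across all T1 variables to predict how many will be flagged, because gender, for example, need not cluster by school as classroom-climate scales do.

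**T1 differences need not be pure chance.** This also stands. Under Recruitment, schools are randomised once they sign the cooperation form, and parental consent is described after that. The Discussion makes teachers responsible for contacting parents. Children without consent receive no questionnaire. Selective recruitment after allocation is possible, so looking at T1 by arm has a purpose. That supports a descriptive or cluster-adjusted comparison. It does not support child-level tests as a way of choosing covariates.

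**A reader might infer that the stated alpha is breached, or that flagged covariates use up the between-school degrees of freedom.** The article does not support either. A high flag rate at T1 is not a type I error rate for the intervention, and the simulation above shows no inflation. The child variables checked at T1 do not each cost a between-school degree of freedom in a child-level mixed model.

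**The stratifier may be left to a fuller plan.** This stands in part. A condensed article can omit such a term, and nothing shows that number of classrooms is prognostic. If it is, omitting it errs on the conservative side. But the article does set out its covariates, and this factor is not among them, so it is worth correcting together with the selection rule.

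**Conclusion.** The point holds in a limited form. Beyond the fixed T1 measure, part of the covariate set depends on tests that use the wrong unit and a criterion unrelated to prognosis. The check flags chance differences more often than 5% for any positive ICC. Over 20 to 100 children per school and ICC 0.02 to 0.10, the rate is about 10% to 55% per clustered variable. That range is assumed and assumes a 5% threshold.

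The consequence is an adjusted model that depends on the data and can change from outcome to outcome. It has not been shown to raise the type I error of the intervention effect. Omitting the stratifier is the weaker half: a possible loss of precision, of unknown size. The point should be dealt with before analysis, but it does not invalidate the trial.

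**What to change.** Change the wording of Statistical analyses as follows.

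1. Do not select covariates by significance tests of T1 differences.
2. Report T1 characteristics and outcomes by arm descriptively, so that readers can still see signs of selective recruitment after allocation. If a formal comparison is wanted for that purpose, adjust it for school clustering and keep it apart from covariate choice.
3. Name one covariate set in advance and use it in every effectiveness model: the T1 value of the outcome, the number-of-classrooms stratum used at randomisation, and a short list of child variables already collected, such as grade and gender.

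No new data are needed and trial conduct does not change. The cost is the rewording plus a few between-school degrees of freedom for the stratum terms. The exact number depends on how many strata were used, which the article does not state.
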